# Monetary incentives and peer referral in promoting digital network-based secondary distribution of HIV self-testing among men who have sex with men in China: study protocol for a three-arm randomized controlled trial

**DOI:** 10.1186/s12889-020-09048-y

**Published:** 2020-06-12

**Keywords:** HIV self-testing, Monetary incentives, Men who have sex with men, Peer referral, Secondary distribution

## Abstract

**Background:**

Human immunodeficiency virus (HIV) testing is a crucial strategy for HIV prevention. HIV testing rates remain low among men who have sex with men (MSM) in China. Digital network-based secondary distribution is considered as an effective model to enhance HIV self-testing (HIVST) among key populations. Digital platforms provide opportunities for testers to apply for HIVST kits by themselves, and secondary distribution allows them to apply for multiple kits to deliver to their sexual partners or members within their social network. We describe a three-arm randomized controlled trial to examine the effect of monetary incentives and peer referral in promoting digital network-based secondary distribution of HIVST among MSM in China.

**Methods:**

Three hundred MSM in China will be enrolled through a digital platform for data collection. The eligibility criteria include being biological male, 18 years of age or over, ever having had sex with another man, being able to apply for kits via the online platform, and being willing to provide personal telephone number for follow-up. Eligible participants will be randomly allocated into one of the three arms: standard secondary distribution arm, secondary distribution with monetary incentives arm, and secondary distribution with monetary incentives plus peer referral arm. Participants (defined as “index”) will distribute actual HIV self-test kits to members within their social network (defined as “alter”) or share referral links to encourage alters to apply HIV self-test kits by themselves. All index participants will be requested to complete a baseline survey and a 3-month follow-up survey. Both indexes and alters will complete a survey upon returning the results by taking a photo of the used kits with the unique identification number.

**Discussion:**

HIV testing rates remain suboptimal among MSM in China. Innovative interventions are needed to further expand the uptake of HIV testing among key populations. The findings of the trial can provide scientific evidence and experience on promoting secondary distribution of HIVST to reach key populations who have not yet been covered by existing testing services.

**Trial registration:**

The study was registered in the Chinese Clinical Trial Registry (ChiCTR1900025433) on 26, August 2019, http://www.chictr.org.cn/showproj.aspx?proj=42001. Prospectively registered.

## Background

### Background and rationale

Men who have sex with men (MSM) are one of the key populations affected by human immunodeficiency virus (HIV) [1]. Compared to general populations, the risk of acquiring HIV is 22 times higher in MSM [2]. In China, the HIV infection rate among MSM was 6.9% by 2018 [3]. Additionally, a large-scale systematic analysis illustrated that prevalence of HIV among MSM in China increased substantially from 2001 to 2018 [4].

HIV testing is considered as a significant stage of the HIV care continuum [5] and the Treat All strategy [6], because serostatus awareness can link patients to timely treatment and prevent wider transmission of HIV [7]. Thus, expanding HIV testing is crucial for HIV prevention and treatment. However, conventional HIV test services like healthcare facility-based tests fail to reach a wider hidden group of people, mainly due to the barriers including the stigma of HIV testing, the lack of confidentiality and privacy, low trust towards healthcare institutions, and inconvenience [8–11]. To increase HIV testing among people who do not know their HIV status, the World Health Organization (WHO) recommends HIV self-testing (HIVST) as an empowering and innovative way to reach those who have limited access to HIV testing and those who are at high risk of HIV infection [12]. With HIVST, individuals can decide where and when to test while ensuring efficiency, privacy, and confidentiality. HIVST may be an effective alternative for those who do not regularly attend healthcare facilities, which may also be a promising approach to increase the uptake of HIV testing in key populations such as MSM [13, 14].

Digital network-based secondary distribution of HIVST could be an effective strategy for promoting HIVST. This is a strategy that individuals (defined as indexes) to apply for multiple HIVST kits and distribute them to their sexual partners or other members (defined as alters) within their social network [14, 15]. A cohort study conducted in Kenya has proven the feasibility and acceptability of secondary distribution of HIVST among female sex workers [14]. One observational study in China also indicated that secondary distribution of HIVST successfully reached people who were not covered by traditional testing services and promoted case identification [16].

Digital health is also considered to be an innovative strategy to deal with traditional health challenges, including challenges for HIV prevention [17]. For example, digital health has been used to promote safe sex, condom use, and awareness of HIV or sexually transmitted diseases among key populations [18, 19]. For MSM, social networking or dating apps are widely used, especially among young MSM, which provides a unique opportunity of leveraging digital health in improving health services among them. Combining digital health and social network-based strategy for HIV testing (i.e., secondary distribution) promotion can help surpass traditional barriers and reach more people who have never been reached by the facility-based services and increase case finding.

In this study, we intend to examine two modified secondary distribution approaches for HIVST through a three-arm randomized controlled trial in Zhuhai, China. The main purpose of this study is to compare the effectiveness of two modified secondary distribution approaches (monetary incentives, and monetary incentives plus peer referral) with the traditional secondary distribution approach, in order to determine whether these two approaches can increase the uptake of HIVST among MSM, especially the first-time testers among alters.

## Objectives

Our trial aims to enable more Chinese MSM to receive HIV self-testing, reach more first-time HIV testing alters, and identify more people with an HIV-positive (reactive) result by implementing the photo-verified HIV self-testing method under different scenarios, i.e., standard secondary distribution, secondary distribution with monetary incentives and secondary distribution with monetary incentives plus peer-referral links.

### Hypotheses

Hypothesis 1: Compared with standard secondary distribution, secondary distribution with monetary incentives will promote index MSM to distribute more HIVST kits to people within their social network.

Hypothesis 2: Compared with standard secondary distribution, secondary distribution with monetary incentives plus peer referral will promote index MSM to distribute more HIVST kits to people within their social network.

Hypothesis 3: Compared with monetary alone secondary distribution, secondary distribution with monetary incentives plus peer referral will promote index MSM to distribute more HIVST kits to people within their social network.

### Trial design

This is a three-arm randomized controlled trial among Chinese MSM. Enrolled indexes will be randomly assigned to one of the three groups: standard secondary distribution, secondary distribution with monetary incentives arm, and secondary distribution with monetary incentives plus peer referral. Further, indexes will be asked to complete a baseline survey at the beginning of the trial, and a three-month follow-up survey after their HIVST kits applications. A flowchart of the trial is shown in Fig. 1.

**Fig. 1 Fig1:**
[figure not shown]
Trial Flow Diagram

## Methods/design

### Study setting and recruitment

This trial, conducted in Zhuhai, is a collaboration among the Social Entrepreneurship to Spur Health (SESH) research team, Zhuhai Center of Diseases Control (CDC), and Zhuhai Xutong Voluntary Services Center (hereafter, Xutong). Zhuhai, located in Southern China, has approximately 17,000 MSM with an HIV prevalence rate of 7% [12]. Xutong is a local gay community-based organization (CBO) founded in 2015 and has developed a digital network-based platform for individuals (all-over time) to apply for free HIV/syphilis self-testing kits provided by Zhuhai CDC. With Xutong’s social impact within the gay community, its volunteers will help with study recruitment, and their online platform will be used to support our intervention implementation.

Study recruitment advertisement will be posted via Xutong’s official account on WeChat, a popular social site in China similar to Facebook and Twitter. The recruitment information will also be advertised on BlueD, the largest social network app within the gay community in China. Potential participants can join the trial via the study ads and sign up for Xutong’s online platform.

### Eligibility criteria

An eligible index is required to meet the following criteria: 1) Chinese born biologically male whose age is 18 years old or older; 2) ever had sex with another man; 3) willing to self-apply HIVST kits via Xutong’s digital platform; 4) willing to provide personal contact information for future follow-up. All participants will need to sign an informed consent electronically before the study.

### Allocation

Randomization will be completed by a computer-generated program with a 1:1:1 allocation ratio. A consented participant will be allocated to one of three study groups, i.e., standard secondary distribution group, secondary distribution with monetary incentives group, and secondary distribution with monetary incentives plus peer referral group.

### Interventions

#### Standard secondary distribution arm/ control arm

Index MSM in this arm will be eligible to apply for up to 5 HIVST kits based on personal needs, and a 100 RMB (≈ 15 USD) deposit will be charged for each kit. The charged deposit will be refunded to the index if anyone (an index himself or alters to whom he distributed) return his/her testing result. In addition, the participants will need to provide contact information for kits shipping. All kits shipped to a participant will be packed with instructions in an unmarked box to protect privacy. Each kit will be assigned with an identical confirmation code for future distribution tracking, and a unique “ST” number for returned results tracking. After receiving kits, an index can choose to use the kits for themselves or distribute additional kits to alters such as sexual partners or friends. Self-testing kit users can photograph and upload their results to the online platform anonymously by scanning the QR code attached on each kit box. Figure 2 shows the HIVST reporting QR code for testers to return results. Further, alters will be asked to fill out a survey regarding their experience of and attitude toward HIVST. After the survey is completed, the deposit will be returned to the matched index by tracking the confirmation code.

**Fig. 2 Fig2:**
[figure not shown]
HIVST Results uploading system

#### Secondary distribution with monetary incentives (SD/monetary incentives) arm

Index MSM in this arm will follow the same application process as in the control arm. Differently, a fixed 20 RMB (≈ 3 USD), designed as the financial incentives, will be offered to all self-testers who report their results. When an alter returns his/her results, his/her matched index MSM will also receive an extra 20 RMB as incentives.

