#### Secondary distribution with monetary incentives plus peer referral (SD/monetary incentives plus peer referral) arm

Index MSM in this arm will first receive the same intervention as the participants received in the monetary incentives arm. In addition, apart from applying for up to five self-testing kits, each index MSM in this arm will obtain a unique referral link, which can be shared with up to 5 individuals within their social network to apply for kits, and each alter can apply for only one kit through the link. Similarly, indexes will be given 20 RMB for each matched alter who returns the result (whether through peer referral or direct distribution). All testers will receive a monetary incentive of 20 RMB once they complete uploading their results.

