### Outcomes

The primary outcomes of this trial consist of three parts: 1) Mean number of motivated alters who have photo-verified self-testing per index in each arm; 2) Proportion of first-time HIV testing among alters in each arm; 3) Proportion of alters with a positive HIV testing result in each arm.

The secondary outcomes of this study consist of three parts 1) Risky sexual behavior among indexes and alters in each arm; 2) Adverse events reported during secondary distribution among indexes and alters in each arm; 3) Attitude towards and past experiences of HIVST and sexual behavior among alters in each arm.

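### Only the two paid arms reward the index for having an upload counted as an alter's, and the photo identifies the kit, not the tester, so any mislabelling of primary outcome 1 would favour H1 and H2

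*Protocol article*

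**What the plan says.** The Outcomes section of the protocol article defines the first primary outcome as "Mean number of motivated alters who have photo-verified self-testing per index in each arm". Whether an upload is classed as the index's own or an alter's therefore decides the count.

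**Control arm.** An index may apply for up to five kits, and "a 100 RMB (≈ 15 USD) deposit will be charged for each kit". He may use kits himself or pass them on. The refund rule is: "The charged deposit will be refunded to the index if anyone (an index himself or alters to whom he distributed) return his/her testing result". On identity at upload: "Self-testing kit users can photograph and upload their results to the online platform anonymously by scanning the QR code attached on each kit box". The Abstract says that the photo shows the used kit with its unique number.

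**Incentives arm.** The application process is the same as in control. A fixed 20 RMB "will be offered to all self-testers who report their results", and "When an alter returns his/her results, his/her matched index MSM will also receive an extra 20 RMB as incentives".

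**Incentives plus referral arm.** "All testers will receive a monetary incentive of 20 RMB once they complete uploading their results". The index also receives 20 RMB for each matched alter, whether reached by a kit he handed over or through his link.

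**Checks.** Under Measures, records are examined and deduplicated by phone number and IP, and staff read the result from the photo. Alters answer a survey when they return a result. The 3-month index survey covers distribution history and the index's relationship to his alters.

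**The concern.** The classification that defines the endpoint is also what triggers a payment, and that payment is assigned by randomisation. A photo of a numbered kit shows that the kit was used. It does not show that the user was someone other than the index. A paid-arm index who tests himself with a spare kit gains by having the upload counted as an alter's; a control index gains nothing from that classification.

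Any mislabelling caused by this difference raises outcome 1 in the paid arms relative to control, which is the direction of H1 and H2. The t-test would then attribute to distribution what is partly labelling. False alters would also bring the index's own testing history and result into primary outcomes 2 and 3, where the direction of the effect is not determined. H3 compares two arms that pay the same premium per alter upload, so the premium by itself gives that comparison no direction.

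**Working it through.** **1. Payment for one upload of the index's own test**, assuming that he also collects the tester's payment (the article does not state how it is paid):

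| Arm | Declared as his own | Declared as an alter's | Gain from relabelling |
|---|---|---|---|
| Control | 100 RMB deposit back | 100 RMB deposit back | 0 |
| Incentives | deposit + 20 | deposit + 20 + 20 | 20 RMB |
| Incentives plus referral | deposit + 20 | deposit + 20 + 20 | 20 RMB |

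For five directly supplied kits, incentive receipts are 5 × 40 = 200 RMB if all are relabelled and 5 × 20 = 100 RMB if none are. The gain is 200 − 100 = 100 RMB.

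**2. Planned differences** (Sample size section: means 0.65, 1.0 and 1.4).
- H1: 1.0 − 0.65 = 0.35.
- H2: 1.4 − 0.65 = 0.75.

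**3. Share of the planned difference.** Let b be the net excess of false alters per index, paid arm minus control. The protocol gives no value, so b is assumed. For example, b = 0.05 arises if 5 in 100 paid-arm indexes relabel one test each, over and above what happens in control.

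| b | b / 0.35 (H1) | b / 0.75 (H2) |
|---|---|---|
| 0.05 | 14% | 7% |
| 0.10 | 29% | 13% |
| 0.20 | 57% | 27% |

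**4. Chance of a false significant result when there is no true effect.** This uses a two-sided test at 0.05 with n = 100 × (1 − 0.20) = 80 per arm, and SE = SD × √(2/n). The rejection probability is 1 − Φ(1.96 − b/SE) + Φ(−1.96 − b/SE). The planned SD is 0.5; 1.0 is shown as an alternative assumption.

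- SD 0.5: SE = 0.5 × √(2/80) = 0.079.
- SD 1.0: SE = 0.158.

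| b | SD 0.5 | SD 1.0 |
|---|---|---|
| 0 | 0.05 | 0.05 |
| 0.05 | 0.10 | 0.06 |
| 0.10 | 0.24 | 0.10 |
| 0.20 | 0.72 | 0.24 |

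At SD 0.5 the probability reaches one half at b = 1.96 × 0.079 = 0.155. If all 100 per arm are analysed at SD 0.5, the last three rows become 0.11, 0.29 and 0.81. The planned comparison is sensitive enough that a small labelling error can matter.

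**The case against.** The strongest reply has four parts.

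- **Mislabelling is not peculiar to the paid arms.** A control index with spare kits has up to 5 × 100 = 500 RMB of deposit to recover, and deduplication could lead him too to upload under another identity. This stands. A reader might infer that own tests are miscounted in the paid arms only; the text does not support that. Only the premium is arm-specific. The incentive is differential, and b has to be read as a net excess.
- **The money is modest and rests on an unstated payment route.** This also stands. A reader might take 200 RMB as the gain, but that is total receipts for five relabelled uploads; the gain over honest labelling is at most 100 RMB. If testers are paid by a route that identifies them, the doubling may not be available and duplicates may be easier to find.
- **There are safeguards.** Deduplication is stated, alters answer a survey, codes link kits to indexes, each link user may apply for one kit, and volunteers contact reactive testers, so some contact route seems to exist. Of these, only phone and IP deduplication is stated as a check for repeated persons. It is hard to square with anonymous upload, and a second phone or connection defeats it. It may also remove genuine alters who test together with the index, a situation that the follow-up survey asks about.
- **An article leaves operating detail to fuller documents.** True, and missing detail is not the point here. The differential payment and the anonymous upload are rules that the article itself states.

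**Conclusion.** The point holds as a risk with a known direction and an unknown size. The article's own rules attach a reward for alter status to the two paid arms and not to control, and the stated verification does not establish that an alter is a different person. Any resulting error in outcome 1 favours H1 and H2.

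The size cannot be derived from the protocol. The 14% to 57% (H1) and 7% to 27% (H2) depend on assumed net excesses of 0.05 to 0.20, and the false-positive probabilities depend further on the SD and the number analysed. Nothing in the document shows that mislabelling has occurred or at what rate, so a reader should not infer that the primary comparison is invalid. What is warranted is a supporting analysis that shows whether the conclusion depends on uploads that may be the index's own.

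**What to change.** The Trial status section says that statistical analysis has not begun, so this can still be fixed in advance with data already planned.

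1. **State one flagging rule for all three arms.** An alter upload is flagged as not shown to be distinct from the index if it shares his phone number or IP, or if the alter's socio-demographic answers (age, sex, marital status, education, income) all match the linked index's baseline answers. Say how phone and IP deduplication works when upload is anonymous.
2. **Report outcome 1 with flagged uploads removed**, as a pre-specified sensitivity analysis beside the primary result. Give the number flagged by each criterion in each arm. If the conclusion on H1 or H2 changes, qualify it.
3. **Use the index's reported distribution history as descriptive support only**, for directly distributed kits and among indexes who answer the survey. It should not cap the count or veto the primary result: it is the same index's self-report, the plan allows for 20% loss to follow-up, and an index may not know who used his link.

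Payments and interventions stay as they are. The cost is a few lines of analysis text and a matching step. The downside is that some genuine alters who resemble the index, or who test together with him, drop out of the sensitivity count. The flag is also imperfect in the other direction, since changing one answer avoids the socio-demographic match, so an unchanged result reassures but does not prove that there was no mislabelling.

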#### Secondary distribution with monetary incentives plus peer referral (SD/monetary incentives plus peer referral) arm

Index MSM in this arm will first receive the same intervention as the participants received in the monetary incentives arm. In addition, apart from applying for up to five self-testing kits, each index MSM in this arm will obtain a unique referral link, which can be shared with up to 5 individuals within their social network to apply for kits, and each alter can apply for only one kit through the link. Similarly, indexes will be given 20 RMB for each matched alter who returns the result (whether through peer referral or direct distribution). All testers will receive a monetary incentive of 20 RMB once they complete uploading their results.

### Follow-up

The follow-up survey will be administered 3 months after indexes apply for HIVST kits. This survey focuses on distribution history, the relationship between indexes and alters, and indexes’ risky sexual behavior. The results from follow-up survey will be compared with baseline survey results to investigate whether the index MSM has changed their behavior after HIVST. Xutong’s volunteers will check returned self-test results. If there is any positive (reactive) result returned, volunteers will contact testers accordingly, and refer them to the local CDC to do confirmation tests. Moreover, reactive testers will be encouraged to distribute HIVST kits to their sexual partners or provide partners’ contact information to volunteers for offering free testing service.

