### Measures

In general, we aim to examine the effectiveness of our modified secondary distribution models. Primary outcomes of this trial are the number of alters, first-time testing alters, and HIV-positive alters in each arm, therefore, all testers’ information will be specifically clarified and recorded. All data will be collected through JINSHUJU, a secure online platform where participants can apply for HIVST kits, report testing results, and complete the baseline and follow-up questionnaires. All data collected from participants will be examined and deduplicated according to phone number and IP.

In the baseline survey, we will collect the socio-demographic characteristics, sexual orientation, sexual behavior, HIV testing history, and social network. When alters return the results, they will also complete a questionnaire online. In this survey, except for basic information on socio-demographic characteristics, sexual orientation, sexual behavior, HIV testing history, and social network will be collected. We will also investigate the attitudes and experiences towards self-test. The follow-up survey for indexes will take place 3 months after the application completed, which focuses on experiences and attitudes on using and distributing self-test kits. The survey mainly inquires about the occurrence of intimate partner violence (IPV) or other adverse events, the relationship between the indexes and the alters, whether indexes have tested together with the alters, and whether indexes have guided the alters on how to perform HIVST.

Specifically, in our surveys, socio-demographic characteristics include indexes’ age, sex, marital status, the highest level of education completed, and monthly income level. Sexual behavior within 3 months includes previous sex with males and females, role during sex with males, condom use, number of sex partners, and drug use. HIV testing history includes health care facility-based and online HIV testing experience. Social network collects community engagements [7], community connectedness [20], identity fusion [21], and social cohesion [22].

All blood samples will be analyzed using *SD Bioline* HIV/Syphilis duo test kits (*SD Bioline Company*, South Korea). Participants will collect fingertip blood samples by themselves according to the instruction. The trained staff of the CDC or CBO will check and read the photos of result and record them in JINSHUJU. The results are subject to the reading of the staff.

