### Trial status

The study timeline was designed from 01, September 2019 to 31, May 2020. At the time of writing this draft protocol, study enrollment and data collection are ongoing. Due to COVID-19 pandemic, study recruitment expects to be delayed till 31, September 2020, and the follow-up will be finished by 31 December 2020. Thus, we have further updated the trial registration status, and updated the study period as 01, September 2019 to 31, December 2020. Ethics approval will be renewed annually. Statistical analysis has not begun. The trial protocol conforms to the Standard Protocol Items: Recommendation for Interventional Trials (SPIRIT) 2013 statement.

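### The planned before-after comparison of index behaviour cannot be attributed to HIV self-testing; it should be descriptive, and the between-arm comparison should adjust for baseline

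*Protocol article*

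**What the plan says.** The Follow-up section sets the purpose of the second index survey: "The results from follow-up survey will be compared with baseline survey results to investigate whether the index MSM has changed their behavior after HIVST". Its timing is given twice, consistently. Follow-up has "The follow-up survey will be administered 3 months after indexes apply for HIVST kits", and Measures has "The follow-up survey for indexes will take place 3 months after the application completed". Measures also gives the recall period for the behaviour items: "Sexual behavior within 3 months includes previous sex with males and females".

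On access to kits, the control arm section says "Index MSM in this arm will be eligible to apply for up to 5 HIVST kits based on personal needs", and the incentives arm section says "Index MSM in this arm will follow the same application process as in the control arm". The third arm receives what the incentives arm receives, plus a referral link. On use, the control arm section says that "an index can choose to use the kits for themselves or distribute additional kits to alters such as sexual partners or friends".

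On calendar time, Trial status says "Due to COVID-19 pandemic, study recruitment expects to be delayed till 31, September 2020" and gives an updated study period of 1 September 2019 to 31 December 2020.

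Separately, Outcomes lists risky sexual behaviour of indexes and alters, by arm, as a secondary outcome. Secondary analysis plans chi-square tests of each such outcome for all three pairs of arms.

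**The concern.** The sentence in Follow-up sets up a contrast within the same men over time and names HIVST as the event that separates before from after. Randomisation does not protect a contrast of that kind. Anything else that changes between the two surveys is part of the result.

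If condomless sex or partner numbers fall for reasons of calendar time, the fall could be presented as a benefit of HIVST. A rise could be presented as risk compensation. Neither reading would have support from the design.

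There is a related, smaller point. The between-arm tests, which the design does support, leave out each index's baseline answer, although the baseline survey collects sexual behaviour.

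**Working it through.** No figure in the protocol bears on this point, so there is none to reproduce. The check has three parts.

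**1. The sections side by side**

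| Needed to attribute a change to HIVST | What the protocol article provides |
|---|---|
| A group without HIVST | None. Indexes in every arm can apply for up to five kits (the three arm sections) |
| A clock that starts at the test | The clock starts at kit application (Follow-up; Measures) |
| Every index exposed | Self-testing by the index is optional (control arm section) |
| Stable background conditions | Study period September 2019 to December 2020, with recruitment delayed by COVID-19 (Trial status) |

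On the clock: a three-month recall taken three months after application reaches back to about the application date. The follow-up answers therefore include the time from application to the test. The article does not give the length of that interval.

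On the calendar: the overlap with the pandemic is at trial level. Each index contributes about three months between application and follow-up, so some men's surveys will straddle the onset and others may fall wholly on one side. The article gives neither an onset date nor enrolment by date, so the number affected cannot be derived.

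**2. Illustration of a shift common to all arms**

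Inputs from Sample size: 100 per arm and 20% loss, so 100 × 0.80 = 80 per arm and 240 in total. Assumed, not in the protocol: a yes/no risk behaviour with 50% prevalence at baseline; half of the men keep their baseline answer and the rest are redrawn; no effect of HIVST or arm; McNemar's test for before-after (the protocol names no test).

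For a 10-point fall, the redrawn men have prevalence 0.50 − 2 × 0.10 = 0.30. Then:

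- P(yes to no) = 0.5 × 0.5 × 0.70 = 0.175, or 42 of 240 men.
- P(no to yes) = 0.5 × 0.5 × 0.30 = 0.075, or 18 of 240 men.
- McNemar statistic at these expected counts = (42 − 18)² / (42 + 18) = 576 / 60 = 9.6, against a critical value of 3.84.
- Approximate power = Φ[(0.10 − 1.96 × √(0.25/240)) / √((0.25 − 0.10²)/240)] = Φ[(0.10 − 0.0633) / 0.0316] = Φ(1.16) = 0.88.

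Simulation with 4,000 runs agrees:

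| Common shift (points) | Before-after, n = 240 | Between arms, 80 v 80 |
|---|---|---|
| 0 | 5% | 4.8% |
| −5 | 35% | 5.0% |
| −10 | 88% | 4.8% |
| −15 | 99.9% | 5.1% |
| −20 | 100% | 5.0% |

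A second set of assumptions (60% baseline, within-person correlation about 0.40, exact McNemar) gives about 26%, 78% and 99% for falls to 55%, 50% and 45% with 240 men. With the 80 men of a single arm it gives about 9%, 29% and 60%. The between-arm test again stays close to 5%.

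In every row with a shift, behaviour really did change. The before-after column is power to detect that change. The only error would be to ascribe it to HIVST.

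**3. What baseline adjustment would add**

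By the linear approximation, adjusting for a baseline value with correlation r to follow-up multiplies the variance of the arm difference by 1 − r². For assumed r of 0.4 and 0.5 this is 1 − 0.16 = 0.84 and 1 − 0.25 = 0.75, a reduction of 16% to 25%.

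**The case against.** The strongest reply has four parts.

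*The randomised question is already covered.* Outcomes and Secondary analysis plan between-arm tests of index risk behaviour. This stands. A reader might infer that any change in index behaviour is uninterpretable, or that the trial fails to ask whether incentives or referral alter behaviour. The documents support neither inference: concurrently randomised arms share the calendar effects, and the between-arm test stays at about 5% whatever the common shift.

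*The sentence in Follow-up is temporal.* It names no test and makes no express causal claim, and the analysis sections contain no before-after test. This also stands, so it would be wrong to say that the plan claims an effect of HIVST. Still, the sentence states the aim of the comparison, ties it to HIVST, and does not call it descriptive.

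*Some threats are conjecture.* Regression to the mean would require that men apply after a riskier spell. The article does not say so, and recruitment is by advertisement. This point therefore does not rest on it.

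*Tested indexes can be identified from returned results, and covariate adjustment is often left to an analysis plan.* The first is true for those who return a result, but they are self-selected and still have no comparator without HIVST. On the second, the article goes beyond silence: it names the chi-square test. That test is valid, and the issue is precision, not bias.

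**Conclusion.** The point holds in a limited form. A baseline-to-follow-up change among indexes can be described, but the design cannot attribute it to HIVST. That rests on four facts stated in the protocol article: access to kits in every arm, timing from application, optional self-testing by the index, and a study period that spans COVID-19. It does not depend on the simulations, whose prevalence, correlation and size of shift are assumed.

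The planned between-arm comparison of index behaviour is sound and gives up some precision by ignoring baseline: about 16% to 25% of variance if the correlation is 0.4 to 0.5, which is also an assumption. The matter concerns a secondary outcome, and the primary outcomes are unaffected. It is worth correcting because Trial status says that analysis has not begun.

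**What to change.** 1. Reword the sentence in Follow-up so that before-after change in index behaviour is reported descriptively only, by arm and by calendar period, with no attribution to HIVST.
2. In Secondary analysis, for index behaviour, replace the unadjusted chi-square with a between-arm model adjusted for the index's own baseline value of the same item, for example logistic regression reported as a standardised risk difference. Keep the same three pairwise contrasts.

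The cost is one reworded sentence and one model per behaviour item, using data that the surveys already collect. The trial gives up any claim about the effect of HIVST itself on index behaviour, which its design could not support.
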